## Background

A large number of patients require cardiac surgery each year and up to 40% of them will experience postoperative delirium [1]. Delirium is a neuropsychological syndrome characterized by fluctuations between acute agitation (hyperactivity) or lethargy (hypoactivity) [2]. According to the Diagnostic and Statistical Manual of Mental Disorders, Fifth Edition (DSM-V), patients may be confused and disoriented [2]. Incoherent speech, visual or auditory hallucinations, and labile emotions may also be observed. Delirium usually results from a mix of predisposing and precipitating factors (e.g., older age, tobacco and/or alcohol consumption, and cognitive decline, as well as surgery, pain, dehydration, and social isolation) [3–5]. Some of these factors can be addressed with preventive clinical interventions, but others cannot and require different approaches to manage and monitor the delirium episode.

Hyperactive delirium requires urgent care because patients may pull out endotracheal tubes or chest drains, injure themselves by falling, and sometimes even sustain fractures. On the opposite extreme, hypoactive delirium may interfere with essential care activities, such as daily breathing exercises, to prevent respiratory infections, or walking exercises to prevent loss of functional abilities. Such clinical complications of delirium contribute to longer length of hospital stay, increased mortality risk, and long-term psycho-functional sequelae [1, 2, 5–7]. Family caregivers of patients with delirium are also greatly affected. Witnessing these behavioral and emotional manifestations of delirium in a loved one has been described by caregivers as highly disturbing, with 75% of families reporting anxiety [8–10].

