**Table 1 Tab1:** **Schedule of enrolment, interventions and assessments**

Study timepoints	Study period: ***A template is adapted from the SPIRIT guidelines***[21]								
	Enrolment	Allocation		Post-allocation					Close-out
	***-t*** _***1***_	0	***t*** _***1***_	***t*** _***2***_	***t*** _***3***_	***t*** _***4***_	***t*** _***5***_	***t*** _***6***_	***t*** _***7***_
Participant timeline	***Delirium onset***		***Day 1***	***Day 2***	***Day 3***	***Day 4***	***Discharge from hospital***	***Day 15***	***Day 30***
*Enrolment:*									
Eligibility screen/Informed consent:									
Caregivers	√								
Patients							√		
Allocation of participants		√							
*Intervention encounters:*									
Control group									
Intervention group			√	√	√		√		
*Assessments:*									
Baseline using a sociodemographic questionnaire	√								
1. Primary Objectives: Acceptability and feasibility of:									
1.1 –the study design	*	*	*	*	*	*	*	*	*
1.2 –the intervention			*	*	*	*	*		
1.3 –rSO2 using the INVOS 5100 device from Covidien, Mansfield MA USA			√	√	√				
2. Secondary Objectives									
H1- Delirium Severity assessed using the Delirium Index scale [22]			√	√	√				
H2- Complications obtained from a keyword search in the medical chart									√
H3- Length of stay obtained from the medical chart									√
H4- Recovery assessed using the Sickness Impact Profile scale [23, 24]									√
H5- Anxiety assessed with the State Trait Anxiety Inventory State [25]	√					√		√	√
H6- Self-efficacy assessed with a scale adapted from Bandura [26]	√					√		√	√

√: Research activity or questionnaire completed at this timepoint.

*: Assessed with indicators detailed in Table 4.

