**Table 2 Tab2:** **Experimental intervention content**

Time of encounter	Summary of content
Pre-bedside visit	• Share knowledge on delirium
	• Share information on present delirium situation (what has the caregiver observed in his/her previous visit and what has the bedside nurse shared with the nurse-mentor)
	• Discuss possible appropriate behaviors to retain (from Table 3)
	• Set a common goal on which behaviors will be adopted by the caregiver (ensure that the behavior agreed on with the caregivers corresponds to his/her abilities)
	• Share examples of the chosen behaviors
Bedside visit	• Nurse adopts discussed behaviors with the patients for the caregiver to observe (role model – vicarious experience of the caregiver)
	• Nurse encourages the caregiver to behave in a similar manner (performance accomplishment)
	• Provide reinforcement and positive feedback (verbal persuasion)
Post-bedside visit	• Nurse provides feedback on behavior
	• Reflect on the bedside visit, on the positive or negative impact of the behavior
	• Prepare for the next visit
	• Sixth encounter: an action plan for the caregiver will be planned with the nurse for the remainder of the patient’s hospital stay
Pre-discharge	• Seventh encounter: nurse, caregiver and patient discuss their experience with delirium

As presented in Table 3, a range of behaviors will be discussed with the caregivers. They will be informed that delirium-related manifestations can fluctuate from one moment to another, that they should plan a range of delirium management behaviors, and that they should be open to the possibility of changing and/or adapting the planned behavior(s) depending on the patient’s condition. A booklet containing examples of behaviors adapted for various delirium situations will be provided by the nurse-mentor, who will facilitate the learning of these behaviors. The caregivers will be encouraged to add any ideas of possible behaviors (e.g., family pictures, sharing a significant personal experience) they may consider appropriate to discuss with the nurse. The intervention content will be adapted according to the evolution of the delirium episode, for instance, if the delirium is resolved before the sixth encounter, the nurse will focus on facilitating general supportive behaviors instead of specific delirium management strategies.

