### Data collection and analysis

#### Statistical methods

The planned analyses concerning all the primary objectives include descriptive statistics, which, along with 95% CI, will be used to portray the intervention and study design’s acceptability and feasibility criteria. Control and experimental group descriptions will be achieved using descriptive statistics reflected by n, mean, standard deviation, and median, minimum, and maximum for continuous variables and frequencies and percentages for categorical variables; 95% CIs will also be presented when appropriate. Finally, to evaluate the validity of cerebral _r_SO_2_, a Pearson or Spearman correlation will be used (depending on level of measurement) to correlate oximetry scores and scores obtained on the ICDSC, DI, and CAM-ICU at Days 1, 2, and 3 following the onset of delirium.

The planned analyses for the study’s secondary objective of preliminary efficacy will include the statistical methods detailed below. It should first be noted that this is a pilot study assessing the feasibility of a larger study and statistical analyses will be used to examine the preliminary effects of the intervention and determine any trend in the results as this study is not powered for statistical testing. For H1 relative to delirium severity, a repeated measure ANCOVA will be performed using the DI scores taken on Days 1, 2, and 3 following delirium onset. The initial scores on the ICDSC taken at delirium onset will be used as a covariate. Post-hoc tests will be performed if the omnibus test is significant for the group by time interaction. Such an interaction would imply that delirium severity is different between groups over the three days. Mixed models will be used so that a patient with missing data at Days 1, 2, and 3 following the onset of delirium will not be excluded from the analysis. The intent-to-treat principle will be respected; all the patients in the study will be included in the analysis according to their group of randomization. Because the pilot study will not be used to definitely assess the efficacy of the intervention (this would be the objective of the larger study), we plan to conduct a sensitivity analysis using the last observation carried forward.

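### The LOCF sensitivity analysis for delirium severity (H1) assumes no change after the last score, although the protocol allows for resolution within the window, and it does not test the mixed model's missing-data assumption

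*Protocol article*

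**What the plan says.** Under Statistical methods, the H1 analysis is set out as follows: "a repeated measure ANCOVA will be performed using the DI scores taken on Days 1, 2, and 3 following delirium onset", adjusted for the ICDSC score at onset. Post-hoc tests follow if the group-by-time interaction is significant. Patients with missing days are kept through the model: "Mixed models will be used so that a patient with missing data at Days 1, 2, and 3" is not excluded. The sensitivity analysis comes next: "we plan to conduct a sensitivity analysis using the last observation carried forward". The only reason offered is pilot status: "Because the pilot study will not be used to definitely assess the efficacy of the intervention".

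Two other places bear on this. Table 1 schedules the Delirium Index on Days 1, 2 and 3 and not at onset. The text under Table 2 (Intervention content) tells caregivers that "delirium-related manifestations can fluctuate from one moment to another", and adapts the intervention "if the delirium is resolved before the sixth encounter". Table 1 places the daily encounters on Days 1 to 3 and Intervention structure runs them at two a day, so resolution before the sixth encounter means resolution within the H1 measurement window.

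**The concern.** LOCF assumes that a patient's severity stays exactly where it was last seen. That fits poorly with an outcome that the protocol allows to resolve during the three days of measurement. Where scores are falling, LOCF holds the missing patients too high. If the two arms differ in how many days are missing, or in how fast they fall, these errors do not cancel, and the group-by-time contrast on which H1 turns is affected.

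There is also a question of purpose. The mixed model relies on scores being missing at random. A useful sensitivity analysis departs from that assumption by a known amount and shows what happens. LOCF swaps in a different and less plausible assumption. Disagreement with the mixed model may then be LOCF's own artefact, and agreement gives little reassurance. Pilot status is not a reason for choosing LOCF.

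What is at stake is the H1 trend that the pilot hands on to the larger trial, and the habit of using LOCF there.

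**Working it through.** **Inputs from the protocol.** Three Delirium Index measurements (Table 1); 30 dyads (Sample size), taken here as about 15 per arm, although randomising blocks of time does not guarantee this. The protocol gives no Delirium Index mean, SD, daily trend or missing rate, and no figure of its own on this point to reproduce.

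**Assumed inputs.** SD 1, correlation 0.5 between days, patients who miss a day stay missing, daily dropout *p* of 10% or 20%, mean fall *d* of 0, 0.25 or 0.5 SD a day, and higher scores meaning worse delirium.

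**Formula.** With Day 1 observed, the LOCF error in an arm's Day 3 mean is

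error = *p* × 2*d* + (1 − *p*) × *p* × *d*

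The first term is patients last seen on Day 1, who miss two days of decline. The second is patients last seen on Day 2, who miss one. The bias in the group difference is the intervention-arm error minus the control-arm error. Day 1 values are not altered, so the same bias passes into the Day 3 minus Day 1 contrast.

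**Results by hand, in SD units.**

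- Flat mean (*d* = 0): error 0 in both arms, bias 0.
- Both arms falling 0.5 a day. At 10%: 0.10 × 1.0 + 0.09 × 0.5 = 0.145. At 20%: 0.20 × 1.0 + 0.16 × 0.5 = 0.280. Equal dropout gives bias 0. Dropout of 10% against 20% gives 0.280 − 0.145 = 0.135, against the arm with more dropout.
- True Day 3 effect of −0.50 (control falls 0.25 a day, intervention 0.5). Control error at 10%: 0.10 × 0.5 + 0.09 × 0.25 = 0.0725. With 10% in both arms the bias is 0.145 − 0.0725 = +0.0725. With 20% in the intervention arm it is 0.280 − 0.0725 = +0.2075. With 20% in control and 10% in intervention it is 0.145 − 0.140 = +0.005.

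**Simulation (15 per arm, 4000 runs), LOCF against a likelihood estimate valid under missing at random.** The ranges cover dropout completely at random and dropout more likely after a low previous score.

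| Scenario | LOCF bias | Likelihood bias (size) |
|---|---|---|
| Flat mean, dropout completely at random | 0.00 to 0.02 in size | 0.00 to 0.02 |
| Flat mean, unequal dropout driven by last score | 0.03 to 0.04 in size | about 0.01 or less |
| Both fall 0.5 a day, 10% v 10% | about 0.00 | 0.01 or less |
| Both fall 0.5 a day, 10% v 20% | 0.09 to 0.13 in size | 0.01 or less |
| True effect −0.50, 10% v 10% | +0.07 to +0.09 | 0.00 |
| True effect −0.50, 20% in intervention arm | +0.21 | 0.02 or less |
| True effect −0.50, 20% in control arm | −0.01 to +0.07 | 0.01 or less |

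Against a true effect of 0.50, a bias of 0.07 to 0.09 is a shrinkage of 14% to 18%, and 0.21 is about 40%. The sampling SD of the LOCF estimate was 0.35 to 0.39, so a bias of 0.09 to 0.13 is about a quarter to a third of the sampling error.

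**Day 1.** Table 1 has no Delirium Index at onset; the onset score used in the model is the ICDSC, a different scale. LOCF therefore has nothing to carry into a missing Day 1.

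**The case against.** The strongest reply is that little depends on this. H1 is a secondary hypothesis in a study that states it is not powered for statistical testing, the main analysis is a mixed model, and LOCF is only a supplement. Some routes to missing data are also closed: patients must spend their full postoperative stay in the study hospital, and those who do not later consent are removed altogether. All of this stands and limits the severity. It does not make LOCF informative.

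Four stronger readings are tempting, and the documents do not support them.

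- *Fluctuation alone makes LOCF biased.* The protocol does describe fluctuation, but variation around a stable mean gives no real bias in the group difference when dropout is completely at random (0.00 to 0.02 SD). Bias needs a mean trend, or dropout tied to the last score and unequal between arms. The support for a trend is the allowance for resolution, which is worded as a possibility.
- *A patient missing Day 1 drops out of the LOCF analysis.* That assumes a complete-case fit, which the protocol does not state. If the same mixed model is fitted after filling, a patient seen on Day 2 or 3 stays in.
- *LOCF understates the standard error.* Simulation of the Day 3 comparison did not show this: the average model-based SE matched the sampling SD (0.365 against 0.365 with a flat mean and equal dropout; 0.389 against 0.388 with decline and unequal dropout).
- *LOCF always favours the arm with fewer missing days.* This holds when both arms fall equally. When trends differ, the net bias can be near zero.

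Nor is it a fault that only one sensitivity analysis is named. An article may leave others to the full plan. The point is that the one it does name is a poor choice.

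**Conclusion.** The concern holds in a limited form. LOCF assumes no change after the last score, in an outcome that the protocol allows to resolve within the measurement window, and it does not vary the assumption on which the mixed model rests. It can bias the group and group-by-time estimates if scores decline and missing days or trends differ between arms. On the assumed inputs the bias is about 0.1 SD with equal trends and unequal dropout, and up to about 0.2 SD when trends also differ. It is near zero with a flat mean, or with equal trends and equal dropout. None of the trend, dropout or correlation values comes from the protocol, so both size and direction are conditional. Severity is minor.

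**What to change.** Replace LOCF with a delta-adjusted analysis. Multiply impute missing Delirium Index scores under the H1 mixed model, shift the imputed values by a small range stated in advance and set separately for each arm, and report the group estimate and 95% CI at each shift. A tipping point is not needed, because an unpowered pilot has no firm conclusion to tip. Alongside it, tabulate missing Delirium Index days and their reasons by arm. Table 4 already tracks the percentage of outcome measures collected and reasons for non-completion of questionnaires, so this is a small extension. The main mixed model stays as it is.

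The cost is a little more programming and a recorded reason for each missing day, with no extra assessments of patients. With about 15 patients per arm the intervals will be wide at every shift.

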### Study objectives and research hypotheses

The primary objective of this pilot study is to examine the acceptability and feasibility of i) the study design; ii) the experimental nursing intervention; and iii) a novel measure, cerebral _r_SO_2_ obtained by NIRS, a non-invasive method to detect cerebral oxygen imbalances among patients with delirium as well as its validity among patients with delirium.

The secondary objective of this pilot study is to examine the preliminary effect of the intervention on patient and caregiver outcomes. The following are the research hypotheses for the study’s secondary objective:

For patient outcomes

Compared with controls, patients in the intervention group will present:

Less severe delirium in the 3 days following onset;Fewer complications (defined as either a sternal wound dehiscence, fall, respiratory tract infection, or accidental removal of urinary catheter, drain, arterial line or endotracheal tube) in the 3 days following onset of delirium;Shorter total length of ICU and total hospital stay;Enhanced psycho-functional recovery one month after the onset of delirium;

For caregiver outcomes

In comparison with controls, caregivers in the intervention group will present:

(H5)A lower anxiety level after the intervention (Day 4 following delirium onset), at Day 15, and at 1 month following delirium onset;(H6)A higher sense of self-efficacy after the intervention (Day 4 following delirium onset), at Day 15, and at 1 month following delirium onset.

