### Sample size

Patients with delirium at either of these post-surgical units will be randomized along with their caregivers to either usual care or experimental group (Table 1). A convenience sample of 30 patient-caregiver dyads will be recruited based on the specific published literature on pilot studies [45–48]. Because of the high involvement needed from caregivers in this intervention, the indicator chosen to determine the feasibility of the study was set as obtaining consent from a proportion of 75% of the caregivers approached to participate in the study. With such a proportion, 30 dyads is a sample large enough to estimate the proportion of caregivers that consent with a precision of ± 15.5% using a 95% confidence interval. In addition, the chosen sample size will enable us to highlight any trend or possible differences in patient and caregiver outcomes between the two study groups.

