For hypothesis H2 on adverse clinical complications following onset of delirium, a combined outcome measure will be used (mention in the hospital chart of sternal wound dehiscence, a fall, respiratory tract infection, or accidental removal of urinary catheter, drain, arterial line or endotracheal tube = yes/no) and groups will be compared using a χ^2^ test.

Student’s T-tests for independent groups will be used for hypothesis involving continuous variables H3 on length of ICU and total hospital stay, H4 on psycho-functional recovery 1 month after the onset of delirium, H5 on caregiver’s anxiety level, and H6 relative to caregiver’s sense of self-efficacy. The planned treatment for missing data for hypotheses H3 to H6 is assigning the value corresponding to the group mean.

Assumptions underlying the planned models will be checked and alternative methods may be used if more appropriate. A significance level of 0.05 will be used for all analyses.

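### H5 and H6 are tested by unadjusted t-tests although caregiver anxiety and self-efficacy are scored at enrolment; H3 total stay needs only a supplementary from-onset summary

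*Protocol article*

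**What the plan says.** **H5 and H6.** The hypothesis for caregiver anxiety concerns the level at follow-up: "A lower anxiety level after the intervention (Day 4 following delirium onset), at Day 15, and at 1 month following delirium onset". Self-efficacy has the same three times. The Statistical methods section assigns Student's t-tests to H3 through H6 in one sentence: "T-tests for independent groups will be used for hypothesis involving continuous variables H3 on length of ICU and total hospital stay", and later in that sentence "H5 on caregiver’s anxiety level, and H6 relative to caregiver’s sense of self-efficacy". No covariate is named. In Table 1, the anxiety and self-efficacy rows are both ticked in the enrolment column, which stands before the allocation column, and again at Day 4, Day 15 and Day 30.

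**H1, for contrast.** The same section gives delirium severity a repeated-measures ANCOVA, fitted by mixed models, with the ICDSC score at onset as covariate.

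**H3.** The hypothesis is "Shorter total length of ICU and total hospital stay". Under Sample size, "Patients with delirium at either of these post-surgical units will be randomized along with their caregivers", and under Randomization a dyad takes the group of the block in which the delirium is detected. The complications hypothesis, H2, is instead counted "in the 3 days following onset of delirium".

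**The concern.** A score taken before allocation on the same scale as the outcome is usually the best single covariate available. The plan collects one for each caregiver outcome and then compares follow-up levels as if it did not exist. In a sample of 30 dyads, a chance difference at enrolment carries over in part into the follow-up difference, and the analysis is meant to look for trends at the 0.05 level to inform a larger trial. An imbalance could be read as a trend, or could hide one, and the effect estimates carried into planning would be less precise than the data allow.

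H3 raises a smaller point of the same kind. Patients enter only once delirium is detected, so total stay includes any days that passed before entry. The intervention cannot affect those days. When delirium begins on the ward, the initial ICU stay is already over.

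**Working it through.** **The plan's own figure.** The only precision figure in the article is for the consent proportion: 1.96 × √(0.75 × 0.25 / 30) = 0.155. This reproduces the stated ± 15.5%. The article gives no figure for H3, H5 or H6.

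**Inputs.** 30 dyads (Sample size). Fifteen per arm is an assumption, since no ratio is stated and block allocation does not guarantee one. The correlation ρ between enrolment and follow-up scores is not given, so 0.3, 0.5 and 0.7 are used as a range.

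**Chance imbalance at enrolment.** The SD of the between-arm difference is √(2/15) = 0.365 SD, with a 95% range of ± 1.96 × 0.365 = ± 0.72 SD. A difference beyond 0.5 SD corresponds to z = 0.5 / 0.365 = 1.37, a two-sided probability of about 17%. An unadjusted comparison carries ρ times the imbalance into the result: at ρ = 0.5, an imbalance of 0.5 SD shifts the follow-up difference by 0.25 SD.

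**Gain from adjustment.** The residual variance is 1 − ρ², the SE is 0.365 × √(1 − ρ²), and the equivalent unadjusted total is 30 / (1 − ρ²). Half-widths use t = 2.05.

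| ρ (assumed) | Variance removed | SE (SD units) | 95% CI half-width | Equivalent unadjusted dyads |
|---|---|---|---|---|
| none (t-test) | 0% | 0.365 | 0.75 | 30 |
| 0.3 | 9% | 0.348 | 0.71 | 33 |
| 0.5 | 25% | 0.316 | 0.65 | 40 |
| 0.7 | 49% | 0.261 | 0.54 | 59 |

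Estimating the slope costs a little. With the factor √(1 + 1/26) = 1.019, the three adjusted SEs become 0.355, 0.322 and 0.266.

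**Block allocation.** A two-week block plus one week of washout makes a three-week cycle. The planned 20 weeks give 20 / 3 ≈ 7 cycles. The figures above treat dyads as individually randomised; with so few blocks, imbalance can be larger.

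**H3.** If time before onset has an SD of 0.5, 1 or 1.5 days (assumed), chance alone gives a between-arm 95% range of 1.96 × 0.365 × SD = ± 0.36, ± 0.72 or ± 1.07 days. The Setting section puts the usual ICU stay at 1 to 2 days and the ward stay at 3 to 4 days.

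**The case against.** **H5 and H6.** These are secondary outcomes in a pilot that says it is not powered for testing, and baseline characteristics will be described, so an imbalance would be partly visible. Both facts stand and limit the weight of the point. The clause allowing alternative methods does not answer it, because it depends on checking model assumptions; a t-test can satisfy all of them and still leave the baseline unused. Nor can the article's brevity explain the gap, since it states a covariate for H1 and an unadjusted test for H5 and H6. A reader might infer that the t-test is biased. It is not: under random allocation, leaving out a baseline covariate costs precision and protection against chance imbalance only.

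**H3.** A reader might infer that H3 should be redefined as stay from onset, with ICU stay restricted to patients in the ICU at onset. The documents do not support this, for four reasons:

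- The plan includes all patients in the analysis by randomised group; the restriction would drop some of them.
- Detected onset is not a neutral starting point. The nurse-mentor is unblinded, and the preliminary results say hypoactive cases are found by speaking to patients with low ICDSC scores. Detection time could therefore differ by arm, whereas total stay does not depend on it.
- The change would alter a stated hypothesis in a trial that is already recruiting.
- The size of the noise is unknown. The article gives neither the spread of time before onset nor the share of ward onsets. It says delirium can appear on waking from surgery, and screening is three times daily in the ICU but only as needed on the ward. Both facts argue against assuming long pre-onset times or many detected ward onsets.

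The article also does not define when the H3 clock starts or whether an ICU readmission counts, so it would be too strong to say that a ward-onset patient's total ICU stay cannot change.

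**Conclusion.** The point holds for H5 and H6 as an avoidable loss of precision and exposure to chance imbalance. The gain from adjustment is small if the correlation is 0.3 and large if it is 0.7. The result rests on 15 dyads per arm, on the assumed correlations, and on the enrolment score being taken before the caregiver knows the group, as the order of columns in Table 1 implies.

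For H3 the supported conclusion is narrower. Total stay mixes days before and after entry, which makes it a blunter measure of what the intervention could change, but it is a defensible outcome and can stay. The size of this effect cannot be settled from the article; the ranges shown also assume independent dyads.

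**What to change.** **H5 and H6.** Replace the t-tests with an ANCOVA at each time, or one mixed model per outcome over Day 4, Day 15 and 1 month, with the enrolment score as covariate. Report the group difference at each time with its 95% CI. If the mixed model is chosen, reword the rule that fills missing H3 to H6 values with the group mean so that it no longer applies to H5 and H6. No new data are needed.

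**H3.** Keep total ICU and total hospital stay in all patients as planned. Add stay from delirium onset as a supplementary descriptive result, with a note that detected onset time could differ by arm because the nurse-mentor is unblinded. Onset is already a study timepoint and length of stay already comes from the chart.

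**Cost.** A change of analysis wording and one extra summary. The article says the outcome analyses are described in the trial registration and that amendments will be communicated there, so the entry should be updated, preferably before group codes are broken.

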#### Randomization

Given the setting of the research center’s ICU and post-ICU surgery wards, with one visitor room shared by both surgical units as the site of the nursing intervention, participant blinding to group assignment is not possible. This poses a risk of inter-group contamination. To reduce this risk, randomization of blocks of time will be used instead of individual randomization. Two-week blocks, followed by a washout period of one week will be assigned to either the control or intervention group. Thus, if a delirium episode is detected during a 2-week block allocated to control, this patient and their caregiver will be assigned to the control group and vice versa. Participants will not be informed of the present allocation of the 2-week block of time until after they have consented to the study. Delirium episodes detected during the 1-week wash out period will not be randomized or included in the study.

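### Filling missing H3–H6 values with the group mean and then running ordinary t-tests makes the standard errors too small and the 0.05 tests too liberal

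*Protocol article*

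**What the plan says.** The Statistical methods section of the protocol article fixes three things for H3 to H6:

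- The test: "T-tests for independent groups will be used for hypothesis involving continuous variables H3 on length of ICU and total hospital stay". The same sentence goes on to cover H4 (recovery at 1 month), H5 (caregiver anxiety) and H6 (caregiver self-efficacy).
- The missing-data rule: "The planned treatment for missing data for hypotheses H3 to H6 is assigning the value corresponding to the group mean".
- The level: "A significance level of 0.05 will be used for all analyses".

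No variance correction, multiple imputation or sensitivity analysis is given for these four hypotheses. H1 is treated differently in the same section: it gets a mixed model so that patients with missing days stay in the analysis.

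Table 1 shows where values can go missing. H3 is read from the medical chart. H4 is a questionnaire at Day 30. H5 and H6 are questionnaires at baseline, Day 4, Day 15 and Day 30. Table 4 lists the questionnaire completion rate and the reasons for non-completion as acceptability indicators, so some loss is foreseen, but no expected rate is stated.

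**The concern.** A value placed exactly at its arm's mean adds to the sample size and degrees of freedom and adds nothing to the sum of squares. A standard t-test cannot tell it from a measured value. The estimated arm difference does not move, but its standard error shrinks, so chance differences cross the 0.05 line more often than the plan says.

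The article wants these tests to show whether there is a trend worth following up. A test that is too liberal makes that signal less trustworthy. An SD computed from the filled data would also be too small, which matters if it is later used in planning.

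**Working it through.** **The plan's own figure.** The only sample-size calculation in the article is for the consent proportion, "with a precision of ± 15.5% using a 95% confidence interval". It reproduces: 1.96 × sqrt(0.75 × 0.25 / 30) = 0.155. It has no bearing on H3 to H6.

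**Inputs**

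- Sample size, from the Sample size section: "A convenience sample of 30 patient-caregiver dyads will be recruited based on the specific published literature on pilot studies".
- Arm sizes: 15 per arm is an assumption. Allocation is by time block ("Two-week blocks, followed by a washout period of one week will be assigned to either the control or intervention group"), so equal arms are not guaranteed.
- Test and level: Student's t-test at 0.05. Two-sided is assumed, since the article does not say.
- Missing values: the number *m* per arm is an assumption and is varied. Values are taken to be missing for reasons unrelated to the outcome.

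**Own-arm mean.** With *m* of 15 filled per arm, the mean difference and the sums of squares equal those of the observed data. The correct analysis has 15 − *m* per arm and 28 − 2*m* degrees of freedom. The planned test uses 15 per arm and 28 degrees of freedom. The t statistic is therefore inflated by

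k = sqrt[ 28/(28 − 2*m*) × 15/(15 − *m*) ]

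and the reported standard error is 1/k of the correct one. The true type I error is 2 × P(T with 28 − 2*m* df > 2.048/k). The SD after filling is sqrt[(14 − *m*)/14] of the observed SD.

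For *m* = 3: k = sqrt(28/22 × 15/12) = sqrt(1.591) = 1.261, so the standard error ratio is 0.79. The cut-off becomes 2.048/1.261 = 1.624 on 22 df, which gives 11.9%. The SD ratio is sqrt(11/14) = 0.886 and the variance ratio is 11/14 = 0.786.

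| Missing per arm | k | SE ratio | True type I error | SD ratio |
|---|---|---|---|---|
| 0 | 1.000 | 1.00 | 5.0% | 1.00 |
| 1 (6.7%) | 1.074 | 0.93 | 6.8% | 0.96 |
| 2 (13%) | 1.160 | 0.86 | 9.0% | 0.93 |
| 3 (20%) | 1.261 | 0.79 | 11.9% | 0.89 |
| 4 (27%) | 1.382 | 0.72 | 15.4% | 0.85 |
| 5 (33%) | 1.528 | 0.65 | 19.7% | 0.80 |

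**Checks on *m* = 3**

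- Simulation with 200,000 replicates gives 11.8% for normal data and 11.6% for lognormal data. Dropping each value at random with probability 20% gives 12.7% (40,000 replicates).
- Observed data only (12 against 12) give 4.98% for normal and 4.4% for lognormal data, with the SD at 0.999 of its true value for normal data.
- How the missing values split between arms changes little: 2 and 4 missing gives 12.0%, 0 and 6 gives 13.0%.
- Small size is not the cause: at 100 per arm with 20% filled the error is 11.7%.

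**Pooled mean of both arms.** Under this other reading, simulated type I error stays at 5.0%. The SD is still about 11% too small (0.890). A true difference is multiplied by 12/15 = 0.80, a dilution of 20%.

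**If the SD were used for planning.** Sample size is proportional to the variance, so a variance ratio of 0.786 cuts it by about 21%. For an assumed difference of 0.5 SD at 80% power, 50 per arm would be planned instead of 63, with true power 70.5%.

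**The case against.** The strongest reply is that little hangs on these tests. H3 to H6 serve the secondary objective, the article disclaims power for them, and definitive efficacy is left to the larger study. The primary analyses are descriptive feasibility and acceptability statistics and oximetry correlations, and the one numerical target is "obtaining consent from a proportion of 75% of the caregivers approached to participate in the study". Mean filling touches none of this, and the estimated arm difference is unchanged. All of that stands and it lowers the severity. It does not make the standard error valid, since tests at 0.05 are still planned and read for trends.

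It can also be said that the article lets the analyst change method after checking assumptions. That sentence concerns the assumptions of the models and does not withdraw the imputation rule.

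Four stronger readings are tempting, and the article does not support them:

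- *The error rate will more than double.* That needs more than two missing of 15 per arm, and no missing rate is stated. H3 comes from charts and should be nearly complete. Under the amended recruitment procedure, dyads whose patient cannot consent before the 1-month assessment are excluded, which may remove some incomplete cases.
- *The larger trial will be undersized.* The article says the pilot leads to a larger powered study. It does not say that an SD from H3 to H6, or one computed after filling, will size it.
- *The 95% confidence intervals are wrong.* Intervals are mentioned for feasibility criteria and group descriptions. None is specified for H3 to H6 differences.
- *The H1 analysis shares the fault.* There the main analysis is a mixed model, and the statement "we plan to conduct a sensitivity analysis using the last observation carried forward" describes only a sensitivity analysis. It does not affect the present point.

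**Conclusion.** The point holds and should be fixed, but it is not critical to the pilot. As written, and read as the arm's own mean, the rule makes the H3–H6 t-tests anti-conservative whenever values are missing.

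The size depends on an unknown missing rate: close to nominal with one missing per arm, about 12% with three, about 20% with five. These figures assume 15 per arm, two-sided tests and missingness unrelated to outcome. Read as the pooled mean, the rule keeps the error rate but dilutes any true difference and still understates the SD. It is therefore unsuitable on either reading.

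In practice the exposure lies with H4 to H6. The consequence for a larger trial is conditional on the filled SD being used to plan it.

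**What to change.** Delete the group-mean sentence. State instead that missing H3–H6 values are not replaced, that each comparison uses the participants with an observed value, and that the number observed and the mean and SD per arm are reported from observed values only.

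For H5 and H6, the kind of mixed model already planned for H1 can be applied to the Day 4, Day 15 and 1-month scores. A caregiver who misses one questionnaire then still contributes the others. This is a natural extension of the plan, but it is not needed to restore the error rate.

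The cost is a change of wording, minor programming and somewhat wider standard errors that reflect the data actually collected. An observed-data comparison gives the same arm difference as own-arm filling, so the point estimate does not change. If missingness is related to outcome, neither approach removes that bias. The completion rates and reasons already planned in Table 4 should be shown beside the results.
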